### Interim analyses {21b}

Not applicable.

### Methods for additional analyses (e.g., subgroup analyses) {20b}

No subgroup analyses are planned.

### Methods in analysis to handle protocol non-adherence and any statistical methods to handle missing data {20c}

The analysis will be done in an intention-to-treat format so that the data from excluded patients are also mentioned in the results. The reason for each patient’s withdrawal, especially the presence of any side effects, will be mentioned in detail. A sensitivity analysis will also be done. Missing data will be checked by multiple imputations.

### Plans to give access to the full protocol, participant-level data, and statistical code {31c}

If there will be logical requests for data in the direction of the present protocol, the corresponding author will send the data set. Otherwise, all information will remain confidential.

## Oversight and monitoring

### Composition of the coordinating center and trial steering committee {5d}

The performance of the researchers and all stages of the study will be under the supervision of the Ethics Committee and the Vice-Chancellor of Isfahan University of Medical Sciences, so that if there is any contradiction with the ethical principles, the preservation of the patient’s health and also the preservation of his human values, the corrections or the termination of this study will be applied.

### Composition of the data monitoring committee, its role and reporting structure {21a}

Data monitoring will be done by the academic committee of Isfahan University of Medical Sciences, which includes impartial and continuous monitoring.

### Adverse event reporting and harms {22}

Any side effects, whether significant or minor, will be reported in full detail though previous studies have reported no adverse effects of selenium supplementation in several types of cancer treated with radiation therapy [43, 44].

### Frequency and plans for auditing trial conduct {23}

The present study will be supervised by the Ethics Committee of Isfahan University of Medical Sciences. Unexpected inspection of the accuracy and correctness of the study and the correct performance of the researchers will be done at least twice during the study.

### Plans for communicating important protocol amendments to relevant parties (e.g., trial participants, ethical committees) {25}

If there is a need for any changes in the study protocol, the changes will be made under the supervision and with the approval of the Ethical Committee of Isfahan University of Medical Sciences. All changes will be reported in detail at https://irct.ir/.

### Dissemination plans {31a}

Final data and results will be presented in official publications.

## Discussion

Thyroid cancer is a common disease worldwide [1, 2]. Inflammation is one of the most important factors causing and worsening thyroid cancer [8–10]. Also, oxidative stress factors are generally high in these patients and are effective in the relapse process [45–48]. The most common treatment solution for these patients is thyroidectomy and then treatment with radioactive iodine to drain thyroid remnants and control metastatic conditions [11–13]. But this solution has many side effects. For example, radioactive iodine, in addition to its beneficial effect on improving cancer, by excessively entering the salivary glands, reduces the secretion of saliva and the annoying mouth dryness [18, 20, 21, 23, 24]. The current solution to improve the salivary secretion of these patients is to use sour candy or chewing gum. But in many patients, this solution does not bring much improvement [27, 28]. Other side effects of RIT include increased oxidative stress and inflammation [26, 45].

Selenium is an essential mineral that affects the metabolism of thyroid hormones, the antioxidant system, and the inhibition of thyroid neoplasm [29, 32, 34, 36]. Selenium can modulate the growth of thyroid cancer cells by stopping the cell cycle and inhibiting cell growth factors. Also, sufficient amounts of this mineral reduce the possibility of DNA damage [36, 49]. Selenium exerts its anti-inflammatory role by modulating inflammatory factors [50, 51]. Selenium, as one of the most important parts of antioxidant selenoproteins, is effective in improving oxidative stress factors [52–55] (Fig. 3).

**Fig. 3 Fig3:**
[figure not shown]
The effect of selenium on salivary glands, inflammatory factors, and oxidative stress in thyroid cancer patients treated with radioactive iodine

Selenium exerts part of its anticancer effects by controlling redox stimuli and thus modulating the redox process [56]. A recent systematic review including 15 articles reported that selenium nanoparticles cause significant cytotoxicity against cancer cells, while normal cells are less affected [57]. Some metabolites derived from selenium, including methyl selenol, can stop the cell cycle in the G1 phase, thus being effective in inhibiting the growth of cancer cells [58].

A review study in 2020 showed that supplementation with 300 to 500 μg/day selenium for a period of 10 days to 6 months without reducing the effectiveness of radiotherapy can reduce the side effects of this therapeutic strategy in several types of cancer treated with radiation therapy. This study did not report any side effects from selenium supplementation [43].

Another review study reported that selenium supplementation reduces ageusia (loss of taste) and dysphagia and diarrhea caused by radiation therapy in various cancers. This supplement did not inhibit the therapeutic effects of radiation therapy and had no side effects [44].

Recently, in a clinical trial study, it was reported that selenium supplementation in thyroid cancer patients treated with radioactive iodine can help maintain salivary gland function. But this study only had 16 patients as a sample size. Also, the effect of selenium on oxidative stress and inflammation has not been investigated [38]. Therefore, the present study will be conducted to investigate the effectiveness of selenium supplementation in patients with PTC treated with radioactive iodine with a larger sample size (*n* = 60).

The main limitation of our protocol is that, due to ethical issues, we will not be able to stop the patients' other medications and study the effect of selenium alone. The solution we have thought of for this limitation is that we will carefully examine all the drugs received by the two groups (selenium receiving group and placebo group) at the beginning and end of the study. Then, if there is a significant difference between the two groups, we will adjust the results.

Another limitation is that due to a lack of funding, it is not possible to consider selenium blood biomarkers to assess adherence to supplements. To control this limitation, the patients will be closely monitored in such a way that the patients will be reminded daily by phone call to take the supplement during the ten days of the intervention. Also, patients return the empty can of the supplement after ten days. In addition, the potential benefits of the current research for patients are described in detail so that patients can cooperate better.

If the present study observes the effectiveness of selenium on thyroid cancer, selenium may be used as a safe supplement with a high potential in improving the symptoms of these patients in the near future.

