**Methods:**

This is a parallel double-blind randomized controlled clinical trial that includes 60 patients aged 20 to 65 years with papillary thyroid cancer (PTC) treated with RAI and will be conducted in Seyyed al-Shohada Center, an academic center for referral of patients to receive iodine, Isfahan, Iran. Thirty patients will receive 200 µg of selenium for 10 days (3 days before to 6 days after RAI treatment) and another 30 patients will receive a placebo for the same period. Sonographic findings of major salivary glands, salivary secretions, and sense of taste will be evaluated before and 6 months after 10-day supplementation.

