### Intervention description {11a}

Both treatment and placebo groups will be treated with radioactive iodine. The treatment group will receive one selenium capsule containing 200 µg of selenium per day for 10 days (3 days before to 6 days after radioactive iodine treatment). The control group will receive a placebo capsule containing 200 µg of maltodextrin per day for 10 days (3 days before to 6 days after radioactive iodine treatment). Selenium capsules are purchased from 21st Century company and the placebo is prepared by the Faculty of Pharmacy of Isfahan University of Medical Sciences. During the intervention, the type and dosage of the drugs used by the patients will not be changed, and the patients will receive all their usual treatments according to the previous routine (under the supervision of a specialist endocrinologist), and receiving selenium or placebo is merely a supplement to the common treatments they receive.

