### Sample size {14}

Since our study is the first in its kind, we calculate the sample size base on CRP as one the most important parameters of this study. Based on a previous study using selenium supplementation on patients with inflammation to reduce inflammatory factors such as CRP [42], and considering 80% power, and the first type error α = 0.05 and the second type error β = 0.20, based on following equation sample size were calculated:$$n\hspace{0.17em}=\hspace{0.17em}2[{(\mathrm{Z}1-\mathrm{\alpha }/2\hspace{0.17em}+\hspace{0.17em}\mathrm{Z}1-\upbeta )}^{2}\hspace{0.17em}\times \hspace{0.17em}{\mathrm{S}}^{2}]/{\Delta }^{2}\hspace{0.17em}\to \hspace{0.17em}2[{(1.96\hspace{0.17em}+\hspace{0.17em}0.84)}^{2}\hspace{0.17em}\times \hspace{0.17em}{(10.9)}^{2}]/{(8)}^{2}$$

A total of 60 subjects (i.e., 30 participants in each group) would be required.

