## Statistical methods

### Statistical methods for primary and secondary outcomes {20a}

In this study, the number of quantitative variables will be reported as mean (standard deviation), and qualitative variables will be reported as number (percentage). The evaluation of the normality of the distribution of quantitative variables will be done using the skewness index and the Q-Q plot diagram. Intra-group analyses will be performed using paired *t*-test and between-group analyses will be performed using independent *t*-test and ANCOVA. The distribution of qualitative variables will be compared between two groups using the chi-square test. SPSS version 22 software will be used to analyze the data with a significance level of *P* < 0.05.

The primary results of this study include the evaluation of CRP and changes in sonographic findings of major salivary glands (including echogenicity, size, margin, and contour in sonography), and the secondary results include the evaluation of the level of taste sensation and secretion of salivary glands by the questionnaire to assess the level of sialadenitis [41].

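### Adjusting for end-of-study drug use whenever the arms differ significantly can bias the selenium effect; adjustment should rest on pre-specified baseline covariates

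*Protocol article*

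**What the plan says.** The rule stands in the Discussion of the protocol article, in the limitations paragraph below Fig. 3. The authors name as their main limitation that the patients' other medication cannot be stopped. Their answer is: "we will carefully examine all the drugs received by the two groups". This is to be done twice, once at the outset and once when follow-up closes. The rule that follows is "Then, if there is a significant difference between the two groups, we will adjust the results".

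Four other places bear on it:

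- **Timing.** Per the Abstract (Methods), outcomes "will be evaluated before and 6 months after 10-day supplementation". The end of the study is therefore about half a year after dosing.
- **Drug stability.** Intervention description {11a} says "During the intervention, the type and dosage of the drugs used by the patients will not be changed". The exclusion for a treatment change (Eligibility criteria {10}) is also limited to the intervention period. That period is 10 days.
- **Model.** Statistical methods {20a} says "between-group analyses will be performed using independent" t-test and ANCOVA. It names no ANCOVA covariates.
- **Principle.** Section {20c} says "The analysis will be done in an intention-to-treat format" and mentions a sensitivity analysis without describing it.

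Nothing limits the drug adjustment to baseline drugs, to particular outcomes, or to a sensitivity analysis.

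**The concern.** The rule joins two different things.

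**End-of-study drugs.** These are measured after randomisation and may respond to treatment. The article's own hypothesis is that radioiodine injures the salivary glands and raises inflammation, and that selenium reduces both. If that is so, patients on selenium might need fewer drugs for these problems by 6 months. The drug comparison would then be significant because the treatment works, and adjusting for drug use would remove part of the effect under test. An intention-to-treat analysis is meant to estimate that total effect.

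**Baseline drugs.** After randomisation, baseline differences are chance. Adjusting for a baseline drug does not condition on anything after randomisation. But if a P-value decides which drugs enter, the final model cannot be known in advance.

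The stated limitation does not need this remedy. Background medication that cannot be stopped is balanced in expectation by randomisation against placebo.

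**Working it through.** **1. Planning figures.** Sample size {14} uses SD 10.9, difference 8, two-sided α = 0.05 and 80% power:

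n = 2 × (1.96 + 0.84)² × 10.9² / 8² = 2 × 7.84 × 118.81 / 64 = 29.1, so 30 per arm and 60 in total.

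The article's figure reproduces; power at 30 per arm is about 81%. The standardised effect is 8 / 10.9 = 0.73 SD. This is a CRP assumption. The article gives no effect size for sonography.

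**2. When drug use reflects the same gland state as the outcome.** Assumed model, 30 per arm, 20,000 simulated trials per cell:

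- Outcome Y = 0.734 × arm + N(0, 1), higher is better.
- Symptom S = −ρ × Y + √(1 − ρ²) × N(0, 1).
- A drug is used if S exceeds a cut-off that gives the placebo use shown below.
- The drug is added as a covariate only if a two-proportion z-test by arm has P < 0.05.

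Average shrinkage of the final estimate from 0.73 SD:

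| Placebo drug use (assumed) | ρ = 0.4 | ρ = 0.6 | ρ = 0.8 |
|---|---|---|---|
| 50% | about 4% | about 12% | about 25% |
| 20% | about 2% | about 6% | about 13% |
| 10% | about 1% | about 3% | about 6% |

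In the 50% row the mean estimates are 0.70, 0.65 and 0.55 SD, and power falls from about 80% to 77%, 71% and 62%. At 50% and ρ = 0.6 the rule fires in about 27% of trials, and the adjusted estimate in those averages 0.57 SD against a true 0.73.

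**3. A second model, on the CRP scale.** SD 10.9, 30 per arm, 4,000 trials per scenario. Assumed placebo drug use is 31% to 36%. Where selenium lowers drug use, it does so by 22 to 24 percentage points.

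| Scenario | True effect | Mean estimate under the rule | Rejection rate under the rule |
|---|---|---|---|
| Selenium lowers drug use; drug use and CRP share a cause | −8 | −6.8 | 0.66 (0.80 unadjusted) |
| Same | 0 | +1.3 | 0.076 |
| Drug use is a mediator worth 5 CRP units | −8 | −7.1 | 0.65 |
| Drug use is a mediator worth 10 CRP units | −8 | −5.9 | 0.48 |
| Selenium does not change drug use | −8 | −8.0 | 0.80 |
| Selenium lowers drug use; drug use unrelated to CRP | 0 | −0.1 | 0.05 |

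The last two rows show the conditions. If selenium does not change drug use, the test fires in about 5% of trials and there is no bias. If drug use is unrelated to the outcome, the rule fires often (70% of trials) and there is still no bias.

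**4. The baseline half.** If k independent baseline comparisons are each made at 0.05, the chance of at least one significant result is 1 − 0.95^k. That is 23% for k = 5 and 40% for k = 10. The article does not say how many drugs or classes will be compared, so k is an assumption. This is a fault of pre-specification, not post-randomisation bias.

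**The case against.** A reader might infer that the rule biases the selenium effect outright. The article does not support that. Bias needs both conditions: selenium must change later drug use, and that use must be related to the outcome. The article documents neither. The only remedies for reduced saliva that it names are sour candy and chewing gum, which are not drugs. The medication it worries about is existing therapy. Section {11d} also says that standard care will not change during the study. All of this stands, and it makes the causal path an assumption. It does not exclude new symptomatic drugs over 6 months, because {11a} and the exclusion criterion stop at the intervention period and {11d} concerns standard care.

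A reader might also take 12% or 25% as the size of the problem. Those values need half of the placebo patients to be on a symptomatic drug, together with a correlation of 0.6 or 0.8. At lower use the shrinkage is small. Nor is it fair to set the adjusted mean against the unadjusted mean in the trials where the rule fires. That unadjusted mean is about 0.89 SD and is itself inflated by selection, since the true value is 0.73.

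Finally, the rule appears as a remark on limitations and not in the statistical methods. It is still a stated rule for the results, and {20a} fixes no covariates that would override it.

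**Conclusion.** The point holds in conditional form. As written, the rule lets a significance test on a post-randomisation variable decide the analysis. It can bias the total effect of selenium if selenium alters later drug use and that use lies on the path to the outcome or shares causes with it. Selecting baseline drugs by significance is a lesser, separate fault.

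The size cannot be derived from the article. Under the first model the average estimate shrinks by about 1% to 25%, for placebo drug use of 10% to 50% and correlations of 0.4 to 0.8. The 0.73 SD effect is borrowed from the CRP planning values. Under the second model a shared cause can also produce a false effect when the true effect is zero. The defect and its remedy do not depend on where in that range the truth lies.

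**What to change.** Replace the conditional-adjustment sentence in the Discussion, and repeat the replacement in Statistical methods {20a}:

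> The primary analysis adjusts only for pre-specified baseline covariates (baseline value of the outcome, age stratum, sex, and any baseline drug named before unblinding), whatever their imbalance. Drugs used during follow-up are described by arm and are not covariates in the primary analysis; any adjustment for them is a labelled sensitivity analysis.

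One precision is needed. Sections {16b} and {17b} keep the labels A and B coded until the statistical analysis is complete. To have any force, *before unblinding* must here mean before any data are tabulated by coded label.

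The cost is one sentence. Age and sex are already the stratification factors in {16a}, and baseline outcome values are already collected. The sample size stays at 30 per arm, and patients are asked for nothing more.

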## Trial status

Version 1, September 2021 Recruitment will be started in February 2023 and approximately will be completed in September 2023.

## Data Availability

If the data request is in the direction of the present protocol, the corresponding author sends the data set. Otherwise, all information will remain confidential.

## Abbreviations

TC: Thyroid cancer
DTC: Differentiated thyroid carcinoma
ATC: Anaplastic thyroid carcinoma
MTC: Medullary thyroid carcinoma
CRP: C-reactive protein
NF-κB: Nuclear factor kappa light chain enhancer of activated B lymphocytes
TKI: Tyrosine kinase inhibitors
RAI: Radioactive iodine
RIT: Radioiodine therapy
TAC: Total antioxidant capacity
SOD: Superoxide dismutase
